## Abstract

**Background:**

Cleansing of the vulva and perineum is recommended during preparation for vaginal delivery, and special attention is paid to cleansing before episiotomy because episiotomy is known to increase the risk of perineal wound infection and/or dehiscence. However, the optimal method of perineal cleansing has not been established, including the choice of antiseptic agent. To address this issue, we designed a randomized controlled trial to examine whether skin preparation with chlorhexidine-alcohol is superior to povidone-iodine for the prevention of perineal wound infection after vaginal delivery.

**Methods:**

In this multicenter randomized controlled trial, term pregnant women who plan to deliver vaginally after episiotomy will be enrolled. The participants will be randomly assigned to use antiseptic agents for perineal cleansing (povidone-iodine or chlorhexidine-alcohol). The primary outcome is superficial or deep perineal wound infection within 30 days after vaginal delivery. The secondary outcomes are the length of hospital stay, physician office visits, or hospital readmission for infection-related complications, endometritis, skin irritations, and allergic reactions.

**Discussion:**

This study will be the first randomized controlled trial aiming to determine the optimal antiseptic agent for the prevention of perineal wound infections after vaginal delivery.

**Trial registration:**

ClinicalTrials.gov NCT05122169. First submitted date on 8 November 2021. First posted date on 16 November 2021

## Administrative information

Note: the numbers in curly brackets in this protocol refer to SPIRIT checklist item numbers. The order of the items has been modified to group similar items (see http://www.equator-network.org/reporting-guidelines/spirit-2013-statementdefning-standard-protocol-items-for-clinical-trials/).

## Background and rationale {6a}

Perineum repair, with or without an episiotomy, is one of the most common surgical procedures for women with damage to the labia, vagina, or perineum during vaginal delivery. Perineal trauma and its repair are strongly associated with postnatal morbidity, including bleeding, infection, pain, urinary and fecal incontinence, and sexual dysfunction [1, 2]. Some studies have shown that episiotomy inevitably leads to an incisional infection [3, 4].

To avoid severe tears and facilitate birth, surgical incision of the perineum (i.e., episiotomy) is often needed before the delivery of the fetal head [5]. Episiotomy rates vary considerably between countries. In Taiwan and China, it has been reported that episiotomy is performed during most vaginal deliveries [6, 7]. However, routine episiotomy is no longer recommended; instead, episiotomy is mainly applied for selective indications such as shoulder dystocia, breech delivery, fetal macrosomia, operative vaginal delivery, persistent occiput posterior position, and a markedly short perineal length [5]. Episiotomy leads to incisional infections due to the specific anatomical position of the incision, which confers susceptibility to vaginal, intestinal, and urethral microbial flora infection [8].

Surgical site infections, which are the second most common type of healthcare-associated infections, are preventable problem that incurs high medical costs. Episiotomy site infection complicates 2.5~9.5% of vaginal deliveries [9, 10]. The skin is a major source of pathogens that cause surgical site infections. The main pathogens involved in perineal infections are *Pseudomonas aeruginosa*, *Escherichia coli*, *Staphylococcus aureus*, and *Staphylococcus epidermidis* [9].

Perineal cleansing before vaginal delivery is one of the steps in preparation for delivery. Perineal antiseptic skin preparation attempts to achieve a sterile field by decreasing the concentration of bacteria colonizing the skin at the episiotomy site. Therefore, optimizing skin antisepsis has the potential to reduce the rate of perineal site infections. However, there is a paucity of information supporting the choice of specific antiseptic agents for vaginal delivery.

### Objectives {7}

The aim of this study is to examine whether skin preparation with chlorhexidine-alcohol is superior to povidone-iodine for the prevention of perineal wound infections after vaginal delivery.

### Trial design {8}

This multicenter, randomized, single-blind placebo-controlled trial (SAVE trial) will enroll women undergoing vaginal delivery. Figure 1 shows a schematic diagram of the study design. After providing written informed consent, women will be randomly assigned to skin antisepsis with chlorhexidine-alcohol or povidone-iodine. Except for the preparation of skin before vaginal delivery, the participants will be treated according to obstetric guidelines at the discretion of the attending physician.

**Fig. 1 Fig1:**
[figure not shown]
Study flowchart

## Methods: participants, interventions, and outcomes

### Study setting {9}

This study will be conducted at the obstetric departments of nine hospitals in South Korea: Asan Medical Center, Ewha Womans University Seoul Hospital, Korea University Guro Hospital, Korea University Anam Hospital, Samsung Seoul Hospital, Seoul National University Hospital, Seoul National University Boramae Medical Center, Seoul National University Bundang Hospital, and Seoul St. Mary’s Hospital. These are all tertiary referral hospitals.

### Eligible criteria {10}

Korean women with term singleton pregnancies who plan to deliver vaginally following episiotomy will be enrolled. The exclusion criteria will be as follows: (1) allergy to chlorhexidine, alcohol, iodine, or shellfish and (2) evidence of infection of the perineum (Table 1). After screening for eligibility, information regarding the study will be provided, and written informed consent will be obtained. The dropout criteria will include the patient’s withdrawal of content, the occurrence of a severe adverse reaction, or a clinical situation that does not permit the continuation of the trial protocol at the discretion of the investigators.

**Table 1 Tab1:** Inclusion and exclusion criteria

Inclusion criteria	Exclusion criteria
Singleton pregnancy Women expecting vaginal delivery after 37 weeks	Allergy to chlorhexidine, alcohol, iodine, or shellfish Women who have evidence of infection of the perineum

### Who will take informed consent? {26a}

Consent for the trial will be obtained in writing using a paper consent form. All pregnant women will be given the opportunity to ask questions prior to completing their consent form. Consent will be obtained by a member of the research team. Prior to randomization, each pregnant women will be checked for eligibility and documented on the checklist.

### Additional consent provisions for collection and use of participant data and biological specimens {26b}

This trial does not involve collection of biological specimens.

### Interventions

#### Explanation for the choice of comparators {6b}

The chlorhexidine-alcohol and povidone-iodine have been approved by Food and Drug as antiseptics for skin. Chlorhexidine and iodine-based preparations have both been shown to decrease bacterial counts and are widely used.

#### Intervention description {11a}

The chlorhexidine-alcohol antiseptic will be 2% chlorhexidine gluconate with 72% alcohol, and the povidone-iodine antiseptic will be 10% povidone-iodine. The eligible participants for the inclusion and exclusion criteria will be randomized into two groups: group 1, chlorhexidine-alcohol group, and group 2, povidone-iodine group.

#### Criteria for discontinuing or modifying allocated interventions {11b}

Participants of the study can withdraw their consent to take part at any time. The principal investigator may exclude patients from the study, if patients’ safety is at risk. In order to generate a meaningful database, excluded patients can be replaced by the recruitment of new patients.

#### Strategies to improve adherence to interventions {11c}

Not applicable as the intervention is performed only once during delivery. Adherence to the follow-up visit schedule is promoted by facilitating the study visit within 3 weeks of after delivery and telephone interview at 4 weeks after delivery.

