### Study outcomes {12}

Data on obstetric and neonatal infection outcomes will be gathered. The primary outcome is the proportion of perineal infections (superficial or deep infections within 30 days of vaginal delivery). Perineal infections will be diagnosed by blinded physicians and verified by medical record review in accordance with the CDC Nosocomial Infections Surveillance System definitions (Table 2). The secondary outcomes are the length of hospital stay, number of office visits, and readmissions for infection-related complications, endometritis, positive culture from wound culture, skin irritation, and allergic reactions (Table 3).

**Table 2 Tab2:** Definition of surgical site infection

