**Superficial incisional surgical site infection**	
*An infection that occurs within 30 days after the operation and involves only skin or subcutaneous tissue at the incision and at least one of the following:* 1. Purulent drainage, with or without laboratory confirmation, from the superficial incision. 2. Organisms isolated from an aseptically obtained culture of fluid or tissue from the superficial incision. 3. At least one of the following signs or symptoms of infection: pain or tenderness, localized swelling, redness, or heat, and the superficial incision is deliberately opened by the surgeon, unless the incision is culture-negative. 4. Diagnosis of superficial incisional surgical site infection by the surgeon or attending physician.	

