### Participant timeline {13}

Participants are recruited into the trial for a total of 4–6 weeks following randomization. The summary of trial procedures is detailed in Fig. 1.

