### Recruitment {15}

The recruitment period is expected to be approximately 42 months (first patient in, to last patient out 43 months). In the study sites, an average of about 180 vaginal deliveries are performed per month. Considering the dropout rate, it was calculated that about 15 patients per institution would be enrolled in 1 month. To cover any unforeseen recruitment difficulties, for example due to the COVID-19 pandemic, 6 extra months of recruitment time were added.

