## Data collection and management

### Plans for assessment and collection of outcomes {18a}

Most of the outcomes are collected in the 4 weeks after delivery with physical exam of the perineum, hospital records, and questionnaires. In cases where participants do not come to a follow-up visit, adherence data will be collected rescheduled outpatient clinic.

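### The primary endpoint runs to day 30 after delivery, but the last dated contact is a telephone interview at 4 weeks (day 28) and the last dated examination is by day 21

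*Protocol article*

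**What the plan says.** **Endpoint.** Under Study outcomes {12} the primary outcome is the proportion of women with "superficial or deep infections within 30 days of vaginal delivery". Table 2 uses the same limit, for example for the superficial form: "An infection that occurs within 30 days after the operation and involves only skin or subcutaneous tissue". Infections are to be diagnosed by blinded physicians and verified by medical record review.

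**Dated contacts.** Under Strategies to improve adherence to interventions {11c}, the article names "the study visit within 3 weeks of after delivery and telephone interview at 4 weeks after delivery". No other section gives a contact with a date.

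**Other statements on follow-up.**
- Plans for assessment and collection of outcomes {18a} gives the period and the sources as follows: "Most of the outcomes are collected in the 4 weeks after delivery with physical exam of the perineum, hospital records, and questionnaires". For missed visits, the same section adds a provision: "In cases where participants do not come to a follow-up visit, adherence data will be collected rescheduled outpatient clinic".
- Participant timeline {13} has this on duration: "Participants are recruited into the trial for a total of 4–6 weeks following randomization". This clock starts at randomization, whereas the endpoint and the contacts are counted from delivery.
- Recruitment {15}: recruitment lasts about 42 months, with "first patient in, to last patient out 43 months". That leaves about one month after the last enrolment.

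**The concern.** A 30-day endpoint needs a source of information that reaches day 30 for every woman. The dated contacts stop earlier. The call is two days short, and the visit is at least nine days short.

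The examination gap matters because of how the endpoint is defined. The Table 2 criteria are purulent drainage, a positive culture, a wound that opens or is opened, a finding on examination, or a physician's diagnosis. A telephone call can prompt any of these but cannot supply them. An infection that starts after the visit is counted only if the woman seeks care or is recalled, and the event reaches a record that the trial reviews.

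A woman who attends the visit and answers the call would not obviously count as missing, so the planned multiple imputation would not cover her. She could be entered as infection-free at day 30 when the last question put to her was on day 28. Missed events lower both infection rates and shrink the absolute difference that the trial is sized to detect.

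**Working it through.** **1. Dates**

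| Item | Day after delivery | Days before day 30 |
|---|---|---|
| Endpoint window closes ({12}, Table 2) | 30 | 0 |
| Telephone interview at 4 weeks ({11c}) | 4 × 7 = 28 | 30 − 28 = 2 |
| Study visit within 3 weeks ({11c}) | 3 × 7 = 21 at the latest | 30 − 21 = 9 or more |

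Days 22 to 28 have the call and records but no dated examination. Days 29 and 30 have no scheduled contact, only records and any unscheduled or rescheduled visit. The participation period does not close the gap by itself. It attaches no contact to its length, and its lower limit is 4 × 7 = 28 days from randomization, which ends no later than day 28 after delivery because randomization comes first.

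**2. The plan's own sample size**

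Inputs from Sample size {14}: rates 6% and 4%, power 80%, type 1 error 0.05 (sidedness not stated; two-sided reproduces the figure), allocation 1:1, dropout 10%. With p̄ = 0.05,

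n per arm = [1.960·√(2·p̄(1−p̄)) + 0.8416·√(p₁(1−p₁) + p₂(1−p₂))]² / (p₁−p₂)²

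= [1.960·√0.0950 + 0.8416·√0.0948]² / 0.02² = (0.6041 + 0.2591)² / 0.0004 = 1862.9, rounded up to 1863.

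Total 2 × 1863 = 3726, and 3726 / 0.90 = 4140. Both match the article.

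**3. Power if a share f of infections is missed equally in both arms**

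The article gives no timing of infections, so f is an assumption. Rates become 0.06(1−f) and 0.04(1−f), with n = 1863 per arm:

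power = Φ{ [(p₁−p₂) − 1.960·√(2p̄(1−p̄)/n)] / √[(p₁(1−p₁)+p₂(1−p₂))/n] }

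For f = 5%: the rates are 5.7% and 3.8%, the difference is 0.0190, and the standard errors are 0.006969 (pooled) and 0.006962 (unpooled). The argument is (0.0190 − 1.960 × 0.006969) / 0.006962 = 0.767, and Φ(0.767) = 77.8%.

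| Share missed, f | Rates | Power |
|---|---|---|
| 0 | 6.0% vs 4.0% | 80.0% |
| 2% | 5.88% vs 3.92% | 79.2% |
| 5% | 5.7% vs 3.8% | 77.8% |
| 6.7% (2/30) | 5.6% vs 3.73% | 77.1% |
| 10% | 5.4% vs 3.6% | 75.5% |

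The 2/30 row assumes a constant hazard over the 30 days and that every infection on days 29 and 30 is lost. In numbers, 1863 × (0.06 + 0.04) = 186.3 infections are expected, of which 2/30 is about 12. If infections cluster early, or records catch late ones, the loss is smaller. The 10% row would need some infections from days 22 to 28 to be missed as well, if the hazard were constant.

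**The case against.** The strongest reply is that the article has ascertainment beyond the two contacts. Infections are diagnosed by blinded physicians and verified in the medical record, hospital records are a named source, missed visits are rescheduled, and participation can run to six weeks. The contacts appear under an adherence heading rather than as the outcome schedule, the flow chart is not available here, and the full protocol may give visit windows around a nominal four weeks.

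Much of this stands, and it rules out several stronger readings.
- **A reader might infer that the end of the window is never observed.** The documents do not support this. Records can capture an event on day 29 or 30, and participation may extend past day 30.
- **A reader might infer that late events rest on unverified recall by women who know their arm, so that the comparison is biased.** Participants are not blinded, but no section lets self-report alone score the endpoint. Blinded diagnosis and record verification are specified.
- **A reader might infer that the follow-up statements contradict one another.** They can all be true together. {18a} speaks of most outcomes, not all, and a visit by week 3, a call at week 4 and four to six weeks of participation are compatible.

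The reply does not remove the gap itself. Record review is described as verifying infections. The article does not say that records are searched through day 30 for every woman, or that care outside the nine hospitals is covered. The rescheduling provision is for women who miss a visit, so a woman who attends on time has no later dated examination. The only dated contacts fall short of the article's own endpoint.

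**Conclusion.** The point holds as a mismatch between the endpoint window and the dated contacts. Days 29 and 30 have no scheduled contact, days 22 to 28 have no dated examination, and the end of the window depends on record review of unstated extent.

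The size is probably modest. The strictly uncontacted part is 2 of 30 days, it is the same in both arms, and it is partly covered by records. Losing every infection in those two days under a constant hazard would cost about 3 percentage points of power (80.0% to 77.1%). The sample size reproduces exactly and carries no margin above 80%, so any loss takes power below target, but nothing here invalidates the comparison. The power figures rest on assumed missed shares, equal in both arms.

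Severity is minor to moderate. Confidence is high on the dates and lower on the consequences, because infection timing is not given and the full protocol may set visit windows.

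**What to change.** 1. Move the closing telephone contact to on or after day 30 from delivery, for example day 30 to 35, and ask about the whole 30-day period.
2. State that the blinded diagnosis and record verification under Study outcomes {12} run through day 30 in both arms. For women already past follow-up, carry out the same record review through day 30, since recruitment is under way.
3. Count the follow-up times in {11c}, {13} and {18a} from delivery, so that they line up with the 30-day endpoint.

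The cost is a wording amendment and a call made a few days later, with no added visit. Last patient out moves by a few days. For women already past follow-up, the record review through day 30 is some extra work.

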#### Relevant concomitant care permitted or prohibited during the trial {11d}

Preexisting perineal infection before delivery is excluded, where additional antibiotics treatment after delivery will be documented.

### Post-trial care {30}

There are no provisions for post-trial care.

### Study outcomes {12}

Data on obstetric and neonatal infection outcomes will be gathered. The primary outcome is the proportion of perineal infections (superficial or deep infections within 30 days of vaginal delivery). Perineal infections will be diagnosed by blinded physicians and verified by medical record review in accordance with the CDC Nosocomial Infections Surveillance System definitions (Table 2). The secondary outcomes are the length of hospital stay, number of office visits, and readmissions for infection-related complications, endometritis, positive culture from wound culture, skin irritation, and allergic reactions (Table 3).

**Table 2 Tab2:** Definition of surgical site infection

**Superficial incisional surgical site infection**	
*An infection that occurs within 30 days after the operation and involves only skin or subcutaneous tissue at the incision and at least one of the following:* 1. Purulent drainage, with or without laboratory confirmation, from the superficial incision. 2. Organisms isolated from an aseptically obtained culture of fluid or tissue from the superficial incision. 3. At least one of the following signs or symptoms of infection: pain or tenderness, localized swelling, redness, or heat, and the superficial incision is deliberately opened by the surgeon, unless the incision is culture-negative. 4. Diagnosis of superficial incisional surgical site infection by the surgeon or attending physician.	
**Deep incisional surgical site infection**	
*An infection that occurs within 30 days after the operation and involves deep soft tissue (e.g., fascial and muscle layers) around the incision and at least one of the following:* 1. Purulent drainage from the deep incision but not from the organ/space component of the surgical site. 2. A deep incision spontaneously dehisces or is deliberately opened by the surgeon when the patient has at least the following signs or symptoms: fever (>38°C), localized pain, or tenderness, unless the site is culture-negative. 3. An abscess or other evidence of infection involving the deep incision is found on direct examination, during reoperation, or by a histopathological or radiological examination. 4. Diagnosis of superficial incisional surgical site infection by the surgeon or attending physician.

**Table 3 Tab3:** Primary and secondary outcomes

Primary outcome (superficial or deep infection within 30 days of vaginal delivery)	Secondary outcome
Proportion of perineal infections	Length of hospital stay Number of office visits and readmissions for infection-related complications
	Endometritis Positive culture from the wound culture Skin irritation Skin allergic reaction

### Participant timeline {13}

Participants are recruited into the trial for a total of 4–6 weeks following randomization. The summary of trial procedures is detailed in Fig. 1.

### Sample size {14}

The sample size was calculated to determine how many participants would be needed to detect a risk reduction from 6% by chlorhexidine-alcohol to 4% by povidone-iodine. We estimated the perineal infection rate as 6% for povidone-iodine, according to our retrospective database. To have 80% power, a type 1 error of 0.05, and a ratio of 1:1 between chlorhexidine-alcohol and 4% by povidone-iodine, a total of 3726 subjects will need to be randomized. To accommodate a 10% dropout rate, 4140 subjects will be enrolled (2070 chlorhexidine-alcohol, 2070 povidone-iodine). The sample size was calculated (PASS 15 (NCSS Statistical Software, USA)) based on the primary endpoint of the study.

### Recruitment {15}

The recruitment period is expected to be approximately 42 months (first patient in, to last patient out 43 months). In the study sites, an average of about 180 vaginal deliveries are performed per month. Considering the dropout rate, it was calculated that about 15 patients per institution would be enrolled in 1 month. To cover any unforeseen recruitment difficulties, for example due to the COVID-19 pandemic, 6 extra months of recruitment time were added.

## Assignment of interventions: allocation

### Sequence generation {16a}

Participants will be assigned to intervention groups at a 1:1 ratio (stratified by the institution) to chlorhexidine-alcohol (group 1) or povidone-iodine (group 2) using an Internet-based randomization system developed and maintained by the Medical Research Collaborating Center (MRCC) of Seoul National University Hospital. To reduce the predictability of random sequence, stratified block randomization method will be used.

